### Sample Size Calculation and Statistical Analysis

We computed the required sample size with the G^*^Power 3.1.9.2 software (Faul et al., 2007; Erdfelder et al., 2009) for the *F*-test. The main endpoint will be the difference in the improvement of the overall score of the IES-R scale. A repeated measure ANOVA will be performed to test differences in the IES-R total scores between groups across the four-time points. The Type I error (α) rate was set at 0.05 (two-sided) and the Power (1 – β) was set at 0.95. The a priori correlation between repeated measures was set at 0.5 and the value of the F was set at 0.25 (*medium* effect size). We found a required sample of 132 subjects. To consider the possibility of attrition, we increased the sample by 14% of the required sample size. The total sample resulted in 150 participants (75 per group). Time will be considered a within-subjects variable, while the type of intervention will be considered a between-subject variable. *Post hoc* comparisons with the Tukey HSD-test will be performed and the effect sizes will be reported in the form of η^2^.

The same analyses will be repeated for all the questionnaires, except the one on the demographic variables. Indeed, as secondary analysis, differences in questionnaire scores between the two groups (i.e., HADS, Distress Thermometer, IES-R, Connor-Davidson Resilience Scale, the UCLA Loneliness Scale) will be assessed using the same analysis of the IES-R scale.

Group differences in questionnaires' measures will be analyzed with *T*-tests, while the chi-square statistic will be used to test the association between treatment groups and socio-demographic variables (gender, age, marital status, and employment status). Correlation analysis will be applied to assess the association between the questionnaires scores across all the time points.

Moreover, the scores of the HADS questionnaire will also be interpreted according to the clinical cutoffs (Annunziata et al., 2020). The scale score reliability (Cronbach α) will also be computed.

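### The named post hoc method, Tukey HSD, contains no comparison of the arms' improvement, and if applied to the eight arm-by-time cells no single error term suits all its pairs

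*Protocol article*

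**What the plan says.** Everything relevant is in the protocol article under Sample Size Calculation and Statistical Analysis.

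- Endpoint: "The main endpoint will be the difference in the improvement of the overall score of the IES-R scale".
- Primary analysis: "A repeated measure ANOVA will be performed to test differences in the IES-R total scores between groups across the four-time points".
- Factors: "Time will be considered a within-subjects variable, while the type of intervention will be considered a between-subject variable".
- Follow-up: "comparisons with the Tukey HSD-test will be performed". The family of means, the error term and any dependence on a significant F-test are not given.
- Planning values: two-sided alpha 0.05, power that "was set at 0.95", and "The a priori correlation between repeated measures was set at 0.5".

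The same analysis is then applied to the other questionnaires, so the follow-up method carries over to every outcome. The Expected Results section restates the hypothesis as a greater improvement in one arm than in the other.

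**The concern.** Tukey HSD compares means two at a time. A difference in improvement between two arms is a contrast of four means: arm A at time t minus arm A at T0, less the same quantity in arm B. The named method therefore does not follow up the hypothesis that the ANOVA is meant to test.

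With assessments at 2 weeks, 4 weeks and 2 months, readers will look to the follow-up tests to learn when the arms differ. If those tests are pairwise cell comparisons, two problems arise. A significant drop in one arm beside a non-significant drop in the other can be mistaken for a treatment effect. And in a mixed design the between-arm and within-person pairs have different standard errors, while HSD uses one.

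**Working it through.** **Inputs.** From the article: 2 arms, 4 times, 75 per arm (150 in total), alpha 0.05 two-sided, correlation ρ = 0.5, f = 0.25, power 0.95. Assumed here: a 0.5 SD arm difference, equal variances and equal correlations over time (compound symmetry), and a range of 0.3 to 0.7 around the stated correlation.

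**The plan's own figure.** With the between-factors formula, λ = f²·N·m/(1+(m−1)ρ) = 0.0625 × 132 × 4/2.5 = 13.2 on 1 and 130 df. Power is 0.9501, which reproduces the stated 132. Then 132 × 1.14 = 150.48, or about 150. This confirms the inputs; it has no bearing on the Tukey step.

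**Which comparisons Tukey can make.**

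- Arm: two levels, one pair, so no multiplicity to adjust for.
- Time means pooled over arms: 4 × 3/2 = 6 pairs, none involving treatment.
- Eight arm-by-time cells: 8 × 7/2 = 28 pairs. Of these, 2 × 6 = 12 are within an arm, 4 compare the arms at the same time, and 12 compare the arms at different times. None is the four-mean contrast.

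**Calibration on the cells.** The 95% studentized range point for 8 means and 3 × 148 = 444 df is 4.307. Dividing by √2 gives a t-equivalent of 3.045, a nominal per-pair level of 0.0023.

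In units of the SD, a between-arm pair has variance 2/n and a within-person pair 2(1−ρ)/n. Using the within-subject error for a between-arm pair shrinks the effective critical value to 3.045 × √(1−0.5) = 2.153, a per-pair level of 0.031 instead of 0.0023. Using the pooled cell error for a within-person pair raises it to 3.045/√0.5 = 4.307, a level of about 0.00002.

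Simulated error under no effect, ungated, 75 per arm (10,000 runs at ρ = 0.5; 6,000 at the other values):

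| Family and error term | ρ = 0.3 | ρ = 0.5 | ρ = 0.7 |
|---|---|---|---|
| 28 cell pairs, within-subject error | 0.12 | 0.20 | 0.36 |
| 4 same-time arm pairs only, within-subject error | 0.05 | 0.10 | 0.24 |
| 28 cell pairs, pooled cell error | 0.032 | 0.022 | 0.020 |
| 4 pooled time means, within-subject error | 0.049 | 0.050 | 0.049 |

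**Power for an assumed 0.5 SD arm difference at one time, ρ = 0.5, 75 per arm.**

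- Tukey over the cells with pooled error: SE = √(2/75) = 0.1633 and 0.5/0.1633 = 3.062. Power = Φ(3.062 − 3.045) = 0.51 (simulated 0.50).
- Baseline-adjusted contrast: SE = √(2(1−0.5²)/75) = √(2 × 0.75/75) = 0.1414 and 0.5/0.1414 = 3.536. At 0.05/3 (critical value 2.394), power = Φ(1.142) = 0.87. At 0.05, power = Φ(3.536 − 1.960) = 0.94.
- Simple change-score contrast: at ρ = 0.5 its variance factor 2(1−ρ) equals 1, so SE = 0.1633. At 0.05/3, power = Φ(3.062 − 2.394) = 0.75.

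The fair comparison is thus 0.51 against 0.87. Of that gap, 0.51 to 0.75 comes from testing 3 contrasts rather than 28 pairs, and 0.75 to 0.87 from baseline adjustment.

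**The case against.** The strongest reply is that the article names only the test. Tukey on the four time means is an ordinary reading, and there it holds its level. The family and error term may be set in a fuller plan that is not shown. This stands: the calibration and power figures are conditional on the cell reading. The mismatch with the endpoint is not, because none of the three possible families contains the difference in change.

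Second, the arms are randomised, so a same-time difference after baseline has the same expectation as the difference in change. Three of the 28 cell pairs (T1, T2, T3) therefore estimate the treatment effect, only less precisely. This also stands. The pairs are inefficient, and they are buried among 25 others that do not estimate it.

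Third, the inflation assumes ungated testing. Over the four same-time arm pairs with the within-subject error, the rate of about 0.10 falls to 0.023 if Tukey follows only a significant interaction F, and to 0.039 after a significant group F. The article states neither gated nor ungated testing.

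A reader might infer more than this supports:

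- That HSD is invalid for repeated measures as such. It is not: on time means under sphericity its error is 0.050.
- That the tests are both too liberal and underpowered. These come from opposite error terms and cannot both occur.
- That the power loss is 0.51 against 0.94. That sets a test corrected for 28 pairs against a single contrast at an uncorrected or gated 0.05.
- That the authors intend to claim a treatment effect from within-arm results. Nothing in the article says so; the wording only leaves the door open.

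**Conclusion.** The point holds as a mismatch between the named follow-up method and the stated endpoint. No Tukey family yields the between-arm difference in improvement. If the eight cells are the family, no one error term serves all 28 pairs: familywise error at ρ = 0.5 and 75 per arm is about 0.20 with the within-subject error and no gate, or about 0.02 with the pooled cell error. In the latter case power is about 0.51, where a baseline-adjusted contrast at 0.05/3 would have about 0.87.

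These sizes rest on the cell reading, compound symmetry and an assumed 0.5 SD difference; only the correlation of 0.5 and the group size come from the article. Tukey is a follow-up step and nothing makes it decide the primary hypothesis, so the error rate of the primary F-test is untouched. The change is worth making before the analysis but does not threaten the trial's main test.

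**What to change.** Replace the Tukey HSD sentence with three prespecified model-based contrasts: the baseline-adjusted difference between arms in IES-R total at T1, T2 and T3, each with a 95% confidence interval. Either adjust the three by Holm, or test them only after a significant primary test, naming the F-test that acts as the gate. Holm is the safer choice, because a gate protects fully only while there is no effect at any time. State that between-arm conclusions rest on these contrasts and not on within-arm tests, and use the same wording for the other questionnaires.

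The cost is analysis wording only. The T0 scores are already collected, and no participants or visits are added. The small downside is that the remaining pairwise cell comparisons become descriptive.

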## Materials and Methods

### Participants and Procedure

Participants will be enrolled through email. Those who will accept to take part in the study will be asked for the signature of the informed written consent. The study will receive ethical approval of the Ethical Committee of the University of the last author of the work. Then, participants will be randomly assigned to one of the two groups. In both groups, participants will receive on their email an invitation for an online platform where they will access the material. Participants will receive weekly reminders via e-mail.

A total of 150 participants (75 per group) will be enrolled based on the following inclusion criteria: (1) cancer patients (illness stage I–II); (2) aged from 18 to 65 years; (3) having an internet connection at home; (4) having a sufficient physical ability (auditory and visual ability) to use a remote internet device; (5) being a proficient Italian speaker; (6) providing the written informed consent. Patients (1) with neurological or psychiatric diseases, (2) hospitalized, and (3) with expertise in relaxation techniques or meditation will be excluded from the study.

Participation in the study will be voluntary, and participants will be allowed to withdraw from the study at any moment. The research protocol follows the CONSORT-EHEALTH V1.6 Guidelines (Eysenbach and CONSORT-EHEALTH Group, 2011). The study will be conducted according to the principles stated in the Declaration of Helsinki (59th WMA General Assembly, World Medical Association, 2008).

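### T-tests of arm differences with no time point or role sit beside the ANOVA for the same scales, and demographics, including continuous age, are tested by arm with chi-square

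*Protocol article*

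**What the plan says.** The Sample Size Calculation and Statistical Analysis section of the protocol article names the IES-R total as the main endpoint and gives one analysis for it: "A repeated measure ANOVA will be performed to test differences in the IES-R total scores between groups across the four-time points". Tukey post hoc comparisons follow. The same analysis is then extended to all the other questionnaires as secondary analysis. One error rate appears, within the sample size calculation: "The Type I error (α) rate was set at 0.05 (two-sided").

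A separate paragraph adds a further set of between-arm tests. "Group differences in questionnaires' measures will be analyzed with" t-tests, and in the same sentence "the chi-square statistic will be used to test the association between treatment groups and socio-demographic variables (gender, age, marital status, and employment status"). No time point, role or error rate is attached to the t-tests. No use is stated for the chi-square results.

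Allocation is random: "Then, participants will be randomly assigned to one of the two groups" (Participants and Procedure). That section also sets the age range at 18 to 65 years. Study Design and Measures has all questionnaires completed at T0 and again at T1, T2 and T3.

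**The concern.** The t-tests can be read in two ways, and neither gives them a useful job.

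- **Post-baseline.** They ask again, scale by scale, the between-arm question already given to the ANOVA. For the IES-R this is the primary question, with no rule on which result counts if the t-tests and the ANOVA disagree. For the other scales they duplicate secondary comparisons only.
- **At T0.** They join the chi-square tests as significance tests of baseline balance. Under random allocation any baseline difference arises by chance, so the null is true by design and the p-value says nothing about whether an imbalance matters for the outcome.

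The chi-square tests of demographics are baseline tests on either reading. For age there is also a mismatch of test and variable: chi-square needs categories, and none are defined.

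At stake are a clear answer to which result is the trial's result, and a baseline table that does not present chance differences as findings.

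**Working it through.** **The plan's own figure.** Inputs from the statistical section: "the value of the F was set at 0.25", "The a priori correlation between repeated measures was set at 0.5", "the Power (1 – β) was set at 0.95", α = 0.05, 2 groups, m = 4 time points.

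- Between-groups effect: λ = f²·N·m / (1 + (m − 1)ρ) = 0.0625 × 132 × 4 / 2.5 = 13.2, df 1 and 130, power 0.9501. N = 130 gives 0.947. The stated 132 is reproduced.
- Group-by-time interaction: λ = f²·N·m / (1 − ρ). This needs only N = 36, so it is not the source of 132.
- Attrition: 132 × 1.14 = 150.48, matching 150.

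The 0.05 was therefore applied to a single F-test in the sizing.

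**Reading 1: post-baseline t-tests on the IES-R.** Null simulation: 20,000 runs, 75 per arm, four visits, normal data, all pairwise correlations 0.5, each test two-sided at 0.05. Applying 0.05 to each t-test is an assumption, since the article states no level for them. Tukey comparisons are not included.

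| Event (at least one p<0.05) | Probability |
|---|---|
| Interaction alone | 0.049 |
| Group effect alone | 0.048 |
| Group effect or interaction | 0.094 |
| Any t-test at T1–T3 | 0.122 |
| Interaction or any T1–T3 t-test | 0.150 |
| Group effect, interaction or any T1–T3 t-test | 0.159 |

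The part due to the t-tests is 0.159 − 0.094 = 0.065. The 0.094 arises without them, because either ANOVA effect could be read as the result. If the interaction alone is taken as the primary test, the rise is from 0.049 to 0.150.

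**Reading 2: tests at T0.** With k independent tests of true nulls, P(at least one p<0.05) = 1 − 0.95^k.

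- Five questionnaires plus four demographics, k = 9: 1 − 0.95⁹ = 0.370.
- HADS subscales counted separately, k = 10: 1 − 0.95¹⁰ = 0.401.
- The four chi-square tests alone, which apply on either reading: 1 − 0.95⁴ = 0.185.

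Independence is generous for related symptom scales. With an assumed common correlation of 0.3 to 0.7 among the six scale scores (not in the documents) and independent demographics, k = 10 gives 0.38 down to 0.32.

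**What a single T0-adjusted model would do.** For illustration, assume a constant 0.4 SD difference at T1–T3, none at T0, ρ = 0.5, and all 75 per arm analysed. The 0.4 is an assumption.

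- ANOVA group effect: the mean of four visits has variance (1 + 3 × 0.5)/4 = 0.625 and the expected difference is 0.3. λ = 0.3² / (2 × 0.625/75) = 5.4, power about 0.64.
- ANOVA interaction: deviations of the visit differences from their mean are −0.3, 0.1, 0.1, 0.1, with sum of squares 0.12. λ = (75/2) × 0.12/0.5 = 9.0, df 3 and 444, power about 0.71.
- T1–T3 mean adjusted for T0: variance (1 + 2 × 0.5)/3 = 0.667, less 0.5² = 0.25 explained by T0, leaves 0.417. λ = 0.4² / (2 × 0.417/75) = 14.4, power about 0.96.

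**The case against.** The pairing of t-tests with demographic tests in one sentence looks like a conventional baseline table, and arm comparisons over time have already been given to the ANOVA. On that view the follow-up reading is the less natural one, and the time point is a detail that a condensed article may leave to the full protocol. This has force: the missing time point alone would not be a finding. The tests themselves are written into the plan, however, and the T0 reading only moves the problem to baseline testing.

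A reader might infer that the primary error rate is 0.16. The article does not support that. It names one endpoint and one analysis, and extra tests do not change that analysis's 5% level unless one is used for the primary conclusion. No passage says one will be, although none rules it out. More than half of the 0.16 also exists without any t-test.

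A reader might also infer that the baseline p-values will decide which covariates enter the model. The plan contains no covariate selection or adjustment step, so that would be speculation. Nor does randomisation guarantee balance; it makes any imbalance a matter of chance. The objection to testing is that the null is known to be true, not that the arms must be alike.

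**Conclusion.** The concern holds in limited form. The plan states a second set of between-arm tests on scales already assigned to the ANOVA, without time point or role, and significance tests of demographics by arm in which age is given a test that does not suit it as written.

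If the t-tests are post-baseline, they add about 6 to 7 percentage points (0.094 to about 0.16) to the null chance of some p<0.05 on the IES-R. This rests on normal data, ρ = 0.5 and 0.05 per test. If they are at T0, the chance of at least one nominally significant imbalance is up to 37–40%, and lower with correlated scales. Neither figure alters the level of the named primary analysis. Severity is minor to moderate: dropping the baseline p-values alone would be only a reporting point, and the larger gain comes from settling on one adjusted comparison.

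**What to change.** - Delete the t-tests of arm differences. If they are kept, state their time point and label them supportive, not to be used for the primary conclusion.
- Present T0 scores and demographics by arm descriptively, without p-values, with age as mean and SD or median and interquartile range.
- Take arm comparisons from one pre-specified model of the T1–T3 scores with the T0 score as covariate, used whatever balance is observed. Name the single contrast that answers the primary question.

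The last item changes the stated analysis, because the ANOVA treats T0 as one of its four outcome times; it does more than remove tests. The cost is a small rewrite of the analysis section. T0 scores are already collected, so no new data are needed, and the sample size stays at 150.

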### Expected Results

We primarily hypothesize a greater improvement in the specific domain of stress symptoms (IES-R) assessed in the group receiving the interactive intervention, compared to the group which will receive only fully automated psychoeducational contents. Secondarily, we expect the same trend of improvement across all the psychological variables in the blended intervention group. Finally, we expect that the blended approach characterized by the presence of both interactive group and relaxation exercises will lead to a relief of the perceived social isolation.

## Discussion

Patients with cancer are immunocompromised and at higher risk of serious illness from infection. Therefore, people adopt behaviors aimed at protecting themselves, such as social distancing; on the other hand, feelings of loneliness and isolation may exacerbate and become burdensome. The limited exposure to social interactions with family, friends, and members of the community can have psychological consequences and lead to poorer mental well-being. A study of the general population also showed loneliness scores in the time of the COVID-19 pandemic resulted to be associated with depressive symptoms and suicidal ideation (Killgore et al., 2020). Furthermore, in cancer patients, delaying testing or clinical procedures might result in enhanced distress (Albano et al., 2020).

Implementing web-based practices on people who are forced into mandatory social isolation may help them become more aware of their mind-body condition and reduce negative effects (Pizzoli et al., 2020a,b). Moreover, relaxation techniques help individuals in achieving a greater state of well-being, increasing the ability to cope with stressful situations (resilience), and strengthening the immune system. Overcoming geographic and mobility problems, both patients and carers using telehealth tools reported a higher perception of social support and more empowerment (Kondylakis et al., 2017; Marzorati et al., 2018).

Remote psychotherapy, and specifically remote Cognitive-Behavioral Therapy, proved to be at least effective as the standard therapy while being less expensive and more accessible than the standard treatments (Richards et al., 2016; Thase et al., 2020). Furthermore, remote therapy might benefit from multiple technological sources to be implemented (e.g., telephone, video, email, audio).

Our results will also suffer from some limitations. Specifically, the comparison between the two groups leads to the analysis of differences between a fixed psychoeducational content and a more interactive and guided one. Thus we will be able to conclude only on the efficacy of a blended intervention vs. a fully automated one, not on the efficacy of the group sessions separately. Furthermore, we planned to include 31 participants per group in the sessions of the blended group, to render the groups more manageable. However, a smaller sample might be more effective and controllable.

There is also the chance that people with a higher propensity to use technology and the internet will agree to take part in the study. Thus, the enrolled sample might be more representative of those who already use technologies and have a good knowledge of digital tools. The same reason might be applied for those who have a positive attitude toward relaxation and meditation. Also, the participants included in the blended groups might be more engaged by groups sessions because of their attitude, thus limiting the generalizability of the results.
